**Methods/design:**

To investigate whether the application of a circular plastic wound protector reduces the rate of surgical site infections in general and visceral surgical patients that undergo midline or transverse laparotomy by 50%. BaFO is a randomized, controlled, patient-blinded and observer-blinded multicenter clinical trial with two parallel surgical groups. The primary outcome measure will be the rate of surgical site infections within 45 days postoperative assessed according to the definition of the Center for Disease Control. Statistical analysis of the primary endpoint will be based on the intention-to-treat population. The global level of significance is set at 5% (2 sided) and sample size (n = 258 per group) is determined to assure a power of 80% with a planned interim analysis for the primary endpoint after the inclusion of 340 patients.

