### Recruitment and trial timeline

A total of 15 centers of general and abdominal surgery in Germany will participate in this trial. The centers vary from university hospitals to community hospitals and include certified centers for colorectal surgery (Darmzentren). All centers are members of the Trial Network (CHIR-*Net*) of the German Surgical Society. Physicians or nurses involved in the trial have been trained in ICH-GCP prior to initiation of the trial. Furthermore, all centers and participants were specifically instructed in study-specific procedures prior to the start of the trial. The centers will be supported by an ICH-GCP qualified flying study nurse from the CHIR-*Net* Surgical Regional Centre Munich to ensure protocol conforming data acquisition and trial interventions. Stratification according to center will be performed and all centers must recruit a minimum of 15 patients.

The duration of the recruitment phase is expected to be 30 months. The last follow-up will be performed a maximum of 45 days after the last patient underwent the trial intervention. Hence, the total duration of the trial is expected to be no longer than 32 months. The study flow is outlined in Figure 2.

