### Statistical methods

#### Sample size calculation

Sample size calculation is based on the primary end point of surgical site infections within 45 days post operation according to the CDC classification [9] and was conducted by using nQuery Advisor software version 7.0 (Statistical Solutions Ltd, Cork, Ireland). Based on the assumption that the percentage of patients developing postoperative wound infections in a mixed surgical population undergoing midline or transverse laparotomy is approximately 16% for the standard group (control group, see Background) and can be reduced to 8% in the experimental intervention arm, a group sample size of 258 patients would need to be compared by the χ^2^ test, to achieve 80% power in detecting this difference in SSI rate at a 2-sided level of significance of 5%. Analysis of the primary efficacy endpoint will be based on a χ^2^ and not based on a random effects model, which would assume different underlying effects within the centers. However a generalized linear mixed effect model (logit link regression) will be fitted to the data in terms of a supportive sensitivity analysis that allows for assessment of the primary efficacy endpoint under consideration of random center effects. Under the assumption of a dropout rate of up to 15%, a total of 600 patients would need to be enrolled in the study. Due to the broad inclusion criteria, the limited number of exclusion criteria, the limited time frame as well as the comprehensible nature of the trial, no more than 200 patients are expected to be screening failures, which brings the total number of patients that need to be screened for eligibility to 800 (Figure 2).

Based on the multicenter trail design, stratification according to recruiting center will be used [46]. Each participating center will have to enroll a minimum of 15 patients. Centers with fewer than 15 patients will be excluded from the primary efficacy analysis. Therefore, recruitment will be continued until enough centers lead to the required total sample size by each enrolling a sufficient number of patients.

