#### Analysis

The primary analysis will be conducted according to the intention-to-treat (ITT) principle, that is, all included patients will be analyzed as randomized. Patients with missing primary outcome data will be considered as non-SSI cases if they belong to the control group and as SSI cases if they were randomized to the innovative treatment arm. For purpose of sensitivity analyses, per protocol and complete case analyses of the primary endpoint will be conducted and further appropriate and less conservative missing-value replacement strategies such as multiple conditional imputation [47] will be employed.

A planned interim analysis will be performed after recruitment and follow-up of 340 patients (two-thirds of the planned total). Due to this intended interim analysis, global α error adjustment is performed by the method of O’Brien and Fleming [48]. Therefore, evaluation of the primary efficacy endpoint will be conducted at a 0.005 level of significance (two sided) in the interim analysis and at a 0.048 level of significance (two sided) in the final statistical analysis.

Prespecified subgroup analyses or treatment group comparisons will be performed for: rate of superficial postoperative SSIs (according to CDC classification); rate of deep postoperative SSIs (according to CDC classification); rate of postoperative SSIs of organ space (according to CDC classification); rate of postoperative SSIs (total/superficial/deep/organ space) stratified by the National Nosocomial Infection Surveillance (NNIS) risk score [46]; rate of postoperative SSIs (total/superficial/deep/organ space) stratified by colorectal and non-colorectal operations.

Secondary analyses will be conducted in an explorative manner. Kaplan-Meier analysis and Cox regression analyses will be employed for analyses of time to event endpoints. The χ^2^ test will be used to compare frequency data between intervention groups. As appropriate, the Student t test, Mann–Whitney U test or analysis of covariance (ANCOVA) will be employed for group comparisons of quantitative data. The 95% confidence intervals will be provided for estimates of relevant effect sizes.

Safety analysis includes description and comparison of the frequency of adverse and serious adverse events in the two intervention groups.

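### Excluding every center with fewer than 15 patients contradicts the stated intention-to-treat primary analysis and discards validly randomized outcomes

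*Protocol article*

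**What the plan says.** The protocol article describes the primary analysis population in three places.

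- **Abstract, Methods/design:** "Statistical analysis of the primary endpoint will be based on the intention-to-treat population".
- **Statistical methods, Analysis:** "The primary analysis will be conducted according to the intention-to-treat (ITT) principle, that is, all included patients will be analyzed as randomized". Patients whose primary outcome is missing stay in, with an imputed value that depends on the arm.
- **Statistical methods, Sample size calculation:** "Each participating center will have to enroll a minimum of 15 patients". Then: "Centers with fewer than 15 patients will be excluded from the primary efficacy analysis". The consequence follows directly: "Therefore, recruitment will be continued until enough centers lead to the required total sample size by each enrolling a sufficient number of patients".

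The primary test is a χ² test. A mixed model with random center effects is only supportive. Randomization is stratified by center and done in blocks (Randomization and blinding). On the number of sites: "A total of 15 centers of general and abdominal surgery in Germany will participate in this trial" (Recruitment and trial timeline).

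**The concern.** The two rules define different primary populations. One keeps every included patient. The other removes whole centers according to how many patients they eventually enrolled. No modified intention-to-treat set is named. None of the listed sensitivity analyses (mixed model, per protocol, complete case, multiple imputation) is said to bring the removed centers back.

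Whether a center reaches 15 is settled only after its patients have been randomized, and many will by then have been operated on and followed. The exclusion is therefore made after randomization, and it falls on patients who may have complete outcomes. Keeping patients with no outcome by imputation while removing patients whose outcome is known is hard to defend.

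Three things are at stake: which set of patients yields the confirmatory p-value, the use of data from people who agreed to be randomized, and the generalizability that the article claims from its pragmatic design and its mix of hospitals.

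**Working it through.** **1. The plan's own figure.** Inputs from Sample size calculation: SSI rates p₁ = 0.16 and p₂ = 0.08, two-sided α = 0.05, power 80%, χ² test. The mean rate is p̄ = 0.12.

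n per group = [z(α/2)·√(2p̄(1−p̄)) + z(β)·√(p₁(1−p₁) + p₂(1−p₂))]² / (p₁−p₂)²

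= [1.960·√0.2112 + 0.842·√0.2080]² / 0.0064 ≈ 257.8, so 258.

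The stated 258 per group (516 in total) is reproduced. It is not affected by this point, and nothing in the formula involves center size.

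**2. The two rules side by side.** Take a center that ends with m patients, where m is between 1 and 14.

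- Under Analysis, all m patients are in the primary analysis, each in the assigned arm.
- Under Sample size calculation, none of the m is in it.

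The rules agree only if no center ends in that range.

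**3. What the exclusion removes.** With k such centers the loss is k·m patients, at most 14k. The article gives neither k nor m. It gives 15 centers and 600 patients, an average of 600/15 = 40 per center. Assuming k = 1 to 5:

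- largest loss: 14 × 1 = 14 to 14 × 5 = 70 patients;
- as a share of 600: 14/600 = 2.3% to 70/600 = 11.7%.

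Because recruitment is to continue until the lost patients are replaced, the cost under the plan as written is up to 14 to 70 extra patients, that is 614 to 670 randomized instead of 600.

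**4. Power if the lost patients were not replaced.** This is not what the plan provides. It shows what the extension of recruitment is protecting. At the final level of 0.048 (z = 1.977), with n per arm equal to half the total:

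power = Φ{[0.08·√n − 1.977·√0.2112] / √0.2080}

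| Patients lost | Example | From 600 randomized | From 516 analyzed |
|---|---|---|---|
| 0 | none | 85.2% | 79.5% |
| 14 | 1 center of 14, or 2 of 7 | 84.4% | 78.4% |
| 28 | 2 of 14, or 4 of 7 | 83.5% | 77.3% |
| 56 | 4 of 14 | 81.6% | 74.8% |
| 70 | 5 of 14 | 80.6% | 73.5% |

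The starting value of 79.5% at 516 comes from using 0.048 instead of 0.05, not from the center rule. The 600 column is closer to the stated analysis, which keeps patients with missing outcomes. It uses the planned rates and ignores the effect of the imputation rule on them.

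**5. Is a minimum center size needed?** Not for the stated primary test: a pooled χ² test uses one 2 × 2 table. The article says explicitly that this test does not rest on a random effects model.

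**The case against.** The best defense is that the rule is fixed in advance, depends on center size and not on arm or outcome, and acts on whole centers. Randomization is blocked within center, so dropping a center removes both arms in nearly equal numbers, apart from incomplete blocks. Outcome assessors and the statistician are blinded. The lost patients are to be replaced. All of this stands, and it limits the point in four ways.

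- **Bias.** A reader might infer that a post-randomization exclusion biases the treatment effect. The article gives no ground for that, and no direction of bias can be shown.
- **Power.** A reader might infer that the trial becomes underpowered. That requires no replacement, contrary to the stated extension of recruitment. Even without replacement, power stays above 80% in every scenario shown when the start is 600; it falls clearly below only from 516.
- **Type of hospital.** A reader might infer that community hospitals would be the ones removed. The article gives no recruitment volumes by type of hospital. It follows only that low-recruiting sites go.
- **Interim.** A reader might infer that centers below 15 would be left out at the 340-patient interim and return at the final analysis. The article does not say how the rule applies at that look, and such detail may sit in the full protocol or the SAP.

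None of this removes the contradiction. Both statements are current text, and the article itself fixes both, so this is not a detail left to another document.

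**Conclusion.** The point holds as a contradiction in the primary analysis population together with an unnecessary exclusion. Followed as written, the center rule yields a primary analysis that is not the stated intention-to-treat analysis whenever a center ends with 1 to 14 patients.

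The size is at most 14 patients per excluded center, lost from the primary analysis and then recruited again. The total rests on an assumed number of small centers, because the article gives none. The remaining harm is reduced generalizability, since low-recruiting sites drop out of a trial whose stated strength is its breadth. The sample size of 258 per group is unaffected.

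**What to change.** Under Sample size calculation, delete the sentence that excludes small centers and the sentence that extends recruitment because of it. State that the primary χ² test includes every randomized patient from every center, at the interim and at the final analysis. Keep 15 per center as a recruitment target only. Add a sensitivity analysis restricted to centers with at least 15 patients.

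Renaming the current set as modified intention to treat, with a justification and a full intention-to-treat analysis beside it, would remove the contradiction in words. It would still leave valid outcomes out of the primary result, so deletion is preferable.

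The cost is a short change of text and no additional data; it saves the replacement recruitment. Trial status reports 323 patients recruited by 29 February 2012, so the change would have to be made as an amendment to a running trial, and before any unblinded analysis.

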#### Analysis

The primary analysis will be conducted according to the intention-to-treat (ITT) principle, that is, all included patients will be analyzed as randomized. Patients with missing primary outcome data will be considered as non-SSI cases if they belong to the control group and as SSI cases if they were randomized to the innovative treatment arm. For purpose of sensitivity analyses, per protocol and complete case analyses of the primary endpoint will be conducted and further appropriate and less conservative missing-value replacement strategies such as multiple conditional imputation [47] will be employed.

A planned interim analysis will be performed after recruitment and follow-up of 340 patients (two-thirds of the planned total). Due to this intended interim analysis, global α error adjustment is performed by the method of O’Brien and Fleming [48]. Therefore, evaluation of the primary efficacy endpoint will be conducted at a 0.005 level of significance (two sided) in the interim analysis and at a 0.048 level of significance (two sided) in the final statistical analysis.

Prespecified subgroup analyses or treatment group comparisons will be performed for: rate of superficial postoperative SSIs (according to CDC classification); rate of deep postoperative SSIs (according to CDC classification); rate of postoperative SSIs of organ space (according to CDC classification); rate of postoperative SSIs (total/superficial/deep/organ space) stratified by the National Nosocomial Infection Surveillance (NNIS) risk score [46]; rate of postoperative SSIs (total/superficial/deep/organ space) stratified by colorectal and non-colorectal operations.

Secondary analyses will be conducted in an explorative manner. Kaplan-Meier analysis and Cox regression analyses will be employed for analyses of time to event endpoints. The χ^2^ test will be used to compare frequency data between intervention groups. As appropriate, the Student t test, Mann–Whitney U test or analysis of covariance (ANCOVA) will be employed for group comparisons of quantitative data. The 95% confidence intervals will be provided for estimates of relevant effect sizes.

Safety analysis includes description and comparison of the frequency of adverse and serious adverse events in the two intervention groups.

Procedures for the statistical analysis of the primary and secondary endpoints will be conducted in line with the ICH-GCP E9 guideline [49]. For the statistical analysis, SAS® software version 9.2 or higher will be used (SAS Institute Inc., Cary, NC, USA). The statistical analysis will be performed by a group-allocation-blinded statistician from the Institute for Medical Statistics and Epidemiology of the TUM.

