### Sample size

A total of 258 patients will be analyzed per group. Given an estimated drop out rate of approximately 15%, 600 patients will be randomized to 1 of the 2 treatment arms.

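### The stated 80% power does not belong to the stated primary analysis: the sample size removes dropouts, while the primary analysis counts missing outcomes against the protector

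*Protocol article*

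**What the plan says.** **Sizing.** The Sample size calculation section assumes that the SSI rate "is approximately 16% for the standard group (control group, see Background) and can be reduced to 8% in the experimental intervention arm". From this it derives 258 per group for a χ² test with 80% power at a two-sided 5% level. It then adds patients for losses: "Under the assumption of a dropout rate of up to 15%, a total of 600 patients would need to be enrolled in the study". The short Sample size section says "A total of 258 patients will be analyzed per group", with dropout put at approximately 15%.

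**Primary analysis.** The Analysis section specifies intention to treat, with every included patient analyzed in the arm assigned. Gaps are filled by arm: "Patients with missing primary outcome data will be considered as non-SSI cases if they belong to the control group and as SSI cases if they" fall in the protector arm. Per-protocol, complete-case and multiple-imputation analyses are listed as sensitivity analyses only. The primary endpoint is tested two-sided, at 0.005 at the interim and "at a 0.048 level of significance (two sided) in the final statistical analysis".

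**The concern.** The two parts of the plan describe different analyses. Enrolling extra patients to finish with 258 per group makes sense if dropouts leave the denominator and the 16% v 8% contrast survives among the rest. The primary analysis keeps those patients and gives each one the value least favorable to the protector, which changes both expected rates and shrinks the contrast. The sample size sections make no allowance for this.

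At stake are the meaning of the 80% and the two-sided error. An effective device could miss significance because of a modest loss of follow-up. A device with no effect could appear harmful more often than the significance level allows.

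**Working it through.** **Inputs from the protocol article.** Control 16%, protector 8%, 258 per group, 80% power, two-sided 5% (Sample size calculation); 600 enrolled, so 300 per arm with balanced groups; final level 0.048 (Analysis).

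**Assumptions added here.** The share m of patients with no primary outcome is equal in the two arms. Patients with missing outcomes have the design rates. Power is for a single test at 0.048, ignoring the small contribution of the interim look.

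**Step 1: reproduce the plan's figure.** With pooled variance and no continuity correction,

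n = [1.960·√(2·0.12·0.88) + 0.842·√(0.16·0.84 + 0.08·0.92)]² / 0.08² = 257.8, so 258 per group.

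Power at 258 per group is 80.0% at 0.05 and 79.5% at 0.048. The sizing arithmetic is sound for an analysis that removes dropouts.

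**Step 2: expected rates under the primary rule.**

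- Control: p_C = 0.16(1 − m)
- Protector: p_T = 0.08(1 − m) + m
- Difference: p_C − p_T = 0.08(1 − m) − m = 0.08 − 1.08m

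The difference is zero at m = 0.08/1.08 = 7.4%, about 22 of 300 patients per arm.

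**Step 3: power for benefit.** With n = 300 and z = 1.977 (two-sided 0.048), power = Φ[(p_C − p_T − z·SE₀)/SE₁]. SE₀ = √(2p̄(1 − p̄)/n) uses the mean rate p̄, and SE₁ = √((p_C(1 − p_C) + p_T(1 − p_T))/n).

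Example at m = 2%: p_C = 15.68%, p_T = 9.84%, SE₀ = 0.02724, SE₁ = 0.02714. Then (0.0584 − 1.977·0.02724)/0.02714 = 0.167, and Φ(0.167) = 57%.

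| Missing per arm | Control | Protector | Power for benefit |
|---|---|---|---|
| 0% | 16.0% | 8.0% | 85% |
| 0.5% | 15.9% | 8.5% | 79% |
| 1% | 15.8% | 8.9% | 73% |
| 2% | 15.7% | 9.8% | 57% |
| 3% | 15.5% | 10.8% | 40% |
| 5% | 15.2% | 12.6% | 15% |
| 10% | 14.4% | 17.2% | 0.2% |
| 15% | 13.6% | 21.8% | about 0% |

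Power falls below 80% at about 0.5% missing, which is 0.005 × 300 = 1.5 patients per arm. At 15% the chance of a significant result against the protector is about 74%. Simulation with 200,000 replicates gives 57% for benefit at m = 2%, 14% at 5%, and 75% for harm at 15%.

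**Step 4: no true effect (16% in both arms).** The rule gives p_C = 0.16(1 − m) and p_T = 0.16(1 − m) + m, a built-in difference of m against the protector. The chance of significant harm is 2.4% at m = 0, 9% at 2% (15.7% v 17.7%) and 35% at 5% (15.2% v 20.2%).

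**The case against.** The strongest defense is that the rule is deliberate. The Analysis section calls its alternatives less conservative, so the authors knew they were guarding against a false claim of benefit. The same section prespecifies complete-case, per-protocol and multiple-imputation analyses, so a reader would see any divergence. The protection against false benefit is real, and so is the transparency. But the 0.005 and 0.048 levels attach to the primary test, and sensitivity analyses do not restore its power. The test is two-sided, and in the direction of harm the rule is anti-conservative.

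The second defense concerns scale, and much of it stands. A reader might infer that the plan expects its result to reverse. The documents do not support that: 15% is given as a dropout ceiling in one place and an approximation in another, never as a rate of missing outcomes. Wounds are documented at six visits, so a patient who leaves early may already have a recorded SSI, and the Discussion aims for complete follow-up. Nor would the result mainly reflect missing data at low loss: at 2% missing, 5.8 of the 8 percentage points remain.

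Two further readings go too far:

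- **Blinding.** The plan says "The statistical analysis will be performed by a group-allocation-blinded statistician", and a reader might infer that this person cannot apply an arm-dependent rule. Data management could apply it before transfer, or it could be run under both labelings of coded groups. The article need not say which, so this is only a note.
- **Death or cancelled surgery.** A reader might infer that these would be scored as SSI in the protector arm. The article does not say that they count as missing outcomes.

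**Conclusion.** The concern holds as a mismatch between the sizing and the primary analysis. The 258 per group and 80% power are correct for an analysis that removes dropouts, and the plan does not make that analysis primary. Even with 300 per arm, power under the stated rule is below 80% once more than about 0.5% of outcomes are missing, and is 57% at 2% and 15% at 5%. Reversal of the expected direction needs more than 7.4% of outcomes truly missing. The 13.6% v 21.8% result, with about a 74% chance of significant harm, is the ceiling case in which all of the 15% dropouts lack an outcome; it is not a forecast.

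The figures rest on the plan's 16% v 8%, 300 per arm, two-sided 0.048, and equal missingness unrelated to outcome. The main conclusion does not depend on the 15%, because a loss of one or two patients per arm already takes power below the stated level.

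**What to change.** Make the multiple imputation already named in the Analysis section, or another less extreme rule, the primary handling of missing outcomes. State that an SSI documented before dropout counts as an event. Keep the complete-case analysis and the arm-dependent worst case as sensitivity analyses.

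This needs a protocol amendment to the analysis text, but no extra patients or data. Timing matters: the article reports 323 patients recruited by 29 February 2012, and the interim is due after recruitment and follow-up of 340. The change should be documented before any unblinded look, including that one.

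The cost is that the primary result then relies on outcomes being missing at random. The retained worst case tests that reliance.

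If the present rule stays primary, restate the power under it for a realistic missing-outcome rate and resize if needed. Resizing works only below 7.4% missing; at or above that share no sample size helps, because no benefit is expected.

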### Stopping guidelines

The trial can be prematurely closed by the coordinating investigator in consultation with the responsible biostatistician for the following reasons: the planned interim analysis indicates that rate or severity of SAE/morbidity in this trial poses a potential health hazard caused by the trial treatment in one or both of the trial groups; it appears that patients' enrolment is unsatisfactory with respect to quality or quantity or data recording is severely inaccurate or incomplete; external evidence demanding a termination of the trial.

In case of premature closure, the ethics committee has to be informed.

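### The interim and final levels of 0.005 and 0.048 are O'Brien-Fleming values for a look at half the information, not at the stated two-thirds; the pair is slightly conservative, but does not match its named method

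*Protocol article*

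**What the plan says.** The abstract fixes the overall error: "The global level of significance is set at 5% (2 sided"). The Sample size section gives the planned total: "A total of 258 patients will be analyzed per group", so 516 in two groups. The Analysis section places the only interim analysis "after recruitment and follow-up of 340 patients (two-thirds of the planned total"). It then names the O'Brien-Fleming method for the alpha adjustment and presents the two levels as its result: "evaluation of the primary efficacy endpoint will be conducted at a 0.005 level of significance (two sided) in the interim analysis and at a 0.048" for the final analysis. The article gives no other information fraction, spending function or reason for these levels.

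The Sample size calculation section assumes that the infection rate "is approximately 16% for the standard group" and "can be reduced to 8% in the experimental intervention arm", with 258 per group "to achieve 80% power in detecting this difference in SSI rate at a 2-sided level of significance of 5"%.

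**The concern.** O'Brien-Fleming levels depend on when the look is taken. The pair 0.005 and 0.048 is the familiar one for two equally spaced looks, but the look here is placed at two-thirds. The method, the timing and the levels are all stated in one paragraph, and they cannot all be right.

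These are the decision thresholds for the primary claim. If the printed numbers and the named method differ, a final p-value lying between the two versions of the final level would be significant under one reading and not under the other. The interim threshold would also be stricter than the method intends at that point.

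**Working it through.** **Inputs.** Overall two-sided alpha 0.05 (abstract); 258 per group (Sample size); rates 16% and 8% (Sample size calculation); one look at 340, method and levels (Analysis).

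**1. Sample size and information fraction.** With mean rate 0.12,

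n = [1.960 × √(2 × 0.12 × 0.88) + 0.842 × √(0.16 × 0.84 + 0.08 × 0.92)]² / 0.08² = 257.8, so 258 per group.

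The plan's figure reproduces. The total is 2 × 258 = 516, and t = 340/516 = 0.659, close to two-thirds (which would be 344). Against all 600 randomized, t would be 340/600 = 0.567, which is not two-thirds.

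**2. Boundaries.** Z1 and Z2 are bivariate normal with correlation √t.

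- Classic O'Brien-Fleming: find c so that P(|Z1| < c/√t and |Z2| < c) = 0.95. The levels are the two-sided p-values of c/√t and c.
- Lan-DeMets O'Brien-Fleming-type spending: spend 2[1 − Φ(2.241/√t)] per side at the look (0.025 per side in total), then solve for the final level.

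| Information at the look | Classic, interim / final | Lan-DeMets, interim / final |
|---|---|---|
| 0.50 | 0.0052 / 0.0480 | 0.0031 / 0.0490 |
| 340/600 = 0.567 | 0.0083 / 0.0469 | 0.0058 / 0.0481 |
| 340/516 = 0.659 | 0.0137 / 0.0453 | 0.0115 / 0.0464 |
| 2/3 | 0.0142 / 0.0452 | 0.0121 / 0.0463 |

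The printed pair is the classic solution at t = 0.50 (c = 1.977, c/√0.5 = 2.797). At t = 0.659 the classic solution is c = 2.002 and c/√t = 2.466. Spending the two-sided 0.05 through a single function instead gives 0.0158 / 0.0442 at t = 0.659, further from the printed pair. The nearest alternative is Lan-DeMets with 600 as denominator, but 0.0058 rounds to 0.006 and 57% is not two-thirds.

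**3. Overall error of the printed pair.** 1 − P(|Z1| < 2.807 and |Z2| < 1.977) is 0.0490 at t = 0.659, 0.0489 at t = 2/3 and 0.0495 at t = 0.567. All are below 0.05. If 0.005 is kept at the look, the final level that uses the full 0.05 is 0.0491 (0.04906 at t = 0.659). Stated as 0.049, the overall error is 0.0499.

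**4. Interim crossing and overall power under 16% versus 8%.** With unpooled variance, the final drift is 0.08/√[(0.1344 + 0.0736)/258] = 2.818, and the interim drift is 2.818 × √0.659 = 2.287. The chance of crossing at the look is 1 − Φ(z1 − 2.287).

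| Levels | z1 | Crossing at the look | Overall power, unpooled / pooled variance |
|---|---|---|---|
| 0.005 / 0.048 (printed) | 2.807 | 30% | 80.1% / 79.5% |
| 0.0115 / 0.0464 (Lan-DeMets) | 2.527 | 41% | 80.0% / 79.4% |
| 0.0137 / 0.0453 (classic) | 2.466 | 43% | 79.8% / 79.2% |
| 0.005 / 0.049 | 2.807 | 30% | 80.3% / 79.7% |

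With pooled variance the first three crossing chances are about 30%, 40% and 42%.

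**The case against.** The strongest reply is that the printed pair is a valid, prespecified boundary. Its overall error is below 5% on every reading of the information fraction, its overall power is about 80%, and a strict interim threshold is a legitimate choice. Restating the levels would buy only a higher chance of crossing early and would lower overall power slightly. All of this stands, and it limits the severity. It does not remove the inconsistency, because the article does not offer the pair as a free choice: it presents the levels as the product of O'Brien-Fleming at this look. Nor does the condensed format explain it, since every element needed for the check is printed.

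Three stronger readings are tempting, and the document does not support them.

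- **A reader might infer that the trial exceeds its 5% error.** It does not. The looser final level is more than offset by the stricter interim level.
- **A reader might infer that the trial is underpowered because 258 per group was sized at 5%.** A single test at 0.048 has 79.5% power against 80.0% at 0.05, but that ignores rejections at the look. Two-look power with the printed pair is 79.5 to 80.1%.
- **A reader might infer that the interim test serves no decision**, because the list introduced by "The trial can be prematurely closed by the coordinating investigator in consultation with the responsible biostatistician for the following reasons" does not mention crossing for efficacy. That is a separate matter of detail. The Analysis section does state an interim test of the primary endpoint, and an article commonly leaves the decision rules to the full protocol.

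**Conclusion.** The point holds as a mismatch between method, timing and levels. For a look at 0.659 of the information, 0.005 is stricter than O'Brien-Fleming gives (0.0115 to 0.0137), and 0.048 is looser (0.0453 to 0.0464). A final p-value between about 0.045 or 0.046 and 0.048 would be judged differently by the printed level and by the named method. The chance of crossing at the look is about 30%, where the named method would give 40 to 43%, and about 0.001 of the 0.05 goes unused.

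Error control and overall power are sound, so the severity is minor to moderate. The figures rest on normal approximations, equal groups, information proportional to patients analyzed, a final analysis of 516, and the plan's own 16% and 8%. If all 600 were analyzed, the classic values would be 0.0083 and 0.0469, which still do not match.

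**What to change.** Settle the levels before any interim data are seen. The Trial status section reports 323 recruited on 29 February 2012, 17 short of the 340 that trigger the look. Either change is enough:

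1. **Keep the method and restate the levels** for the actual information fraction: about 0.014 and 0.045 (classic), or 0.0115 and 0.046 (Lan-DeMets spending), saying which version is used. Cost: two numbers and a sentence, a slightly tighter final test, and 0.1 to 0.3 percentage points of overall power.
2. **Keep 0.005 at the interim and set the final level at 0.049** (solution 0.0491; 0.049 stays just under 5% overall), and no longer describe the pair as O'Brien-Fleming values for this timing. Cost: one number and a sentence. Overall power rises by about 0.2 points, and the chance of crossing at the look stays at about 30%.

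Neither option changes the sample size.
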